### 5.2. Data Analysis

The baseline data of the treatments and control groups will be compared using the chi-squared test for binary variables and the independent sample t-test for continuous variables. To prevent overestimating the impact of both interventions, an intention-to-treat approach will be assumed to evaluate the impact on the primary and secondary outcomes. The comparison between the treatment groups versus control groups over time (differences between and within) will be performed through mixed general linear models of analysis of variance for repeated measures. Effect sizes (Cohen’s d coefficient) will also be provided between T0 and T1, T1 and T2, and T0 and T2 to determine if the intervention shows any treatment effect. A significance level of 0.05 will be set for a two-sided test, and the 95% confidence interval will be calculated. In addition, time to complete wound healing and time to favorable healing prognosis (based on the wound size) will be estimated using survival analysis, specifically, single variable and multivariable Cox proportional hazard ratio regression models and Kaplan–Meier plots. All previous analyses will include the DFU stage at the baseline as a control variable. Other confounding clinical factors associated with the outcome variables will also be considered in the statistical analysis.

The data will be analyzed using the Rstudio, R version 3.6.2 (R Core Team, Vienna, Austria) and the SPSS statistics, v. 24.0 (IBM Corp., Armonk, New York, NY, USA).

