#### Primary Specific Aims

The primary specific aims of this RCT are: (i) to compare the impact of both treatment groups (TG1 and TG2) in regard to DFU healing, physiological indicators of healing prognosis (biochemical parameters, inflammatory and angiogenic markers, miRNAs, and immune cells), and QoL, compared to control groups; (ii) to compare patients pre and post-intervention in the TG1 and TG2, controlling for patients’ health literacy, clinical characteristics (e.g., duration of diabetes and DFU, type of diabetic foot), and sociodemographic variables (e.g., gender, age, education, socioeconomic level); and (iii) to compare the efficacy of TG1 and TG2 versus ACG to DFU healing, according to participants and their respective family caregiver’s perceptions.

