## 3. Outcomes and Measures

### 3.1. Participant Timeline

Participants in the intervention and control groups will be assessed at the pre-intervention baseline (T0), at the end of the intervention/two months later at post-test (T1), and six months after T1 at the follow-up (T2). Data will be collected through face-to-face interviews conducted by health psychologists (Researchers 1, 2, and 3). Regarding the biochemical sample collection (biochemical parameter, inflammatory and angiogenic markers, miRNAs, and immune cells), a blood sample will be collected during the consultation at the T0, T1, and T2 assessment moments (Table 1).

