### 3.3. Measures of Primary Outcomes

Primary outcomes are DFU healing, physiological indicators of healing prognosis, DFU impact on QoL, and physical and mental QoL.

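### The repeated-measures comparison over T0, T1 and T2 does not adjust for the T0 value of the outcome, so a valid group-by-time test is less precise than the data allow

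*Protocol article*

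**What the plan says.** Section 5.2 (Data Analysis) gives the model for the main comparison, a repeated-measures ANOVA: "The comparison between the treatment groups versus control groups over time (differences between and within) will be performed through mixed general linear models of analysis". Section 3.1 (Participant Timeline) defines three assessments and says that participants "will be assessed at the pre-intervention baseline (T0"), then at T1 and T2. Cohen's d "will also be provided between T0 and T1, T1 and T2, and T0 and T2".

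On covariates, 5.2 says "All previous analyses will include the DFU stage at the baseline as a control variable", and then "Other confounding clinical factors associated with the outcome variables will also be considered in the statistical analysis". Aim (ii) under Primary Specific Aims is "to compare patients pre and post-intervention in the TG1 and TG2, controlling for patients" health literacy and clinical and sociodemographic characteristics. None of these places names the T0 value of the outcome being analysed.

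The model has to serve several outcomes. Section 3.3 reads: "Primary outcomes are DFU healing, physiological indicators of healing prognosis, DFU impact on QoL, and physical and mental QoL". Table 1 schedules all of them at T0, T1 and T2.

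No sentence states outright that T0 is a level of the response. It follows from the three assessments, the within-group part of the comparison, the effect sizes that start from T0, and the pre/post aim. Section 5.2 does not say whether the group term or the group-by-time term carries the treatment comparison.

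**The concern.** T0 is measured before treatment, so randomisation makes the expected group difference there zero. A repeated-measures ANOVA that treats T0 as one more response level does not use that knowledge. Its group-by-time term sets the later visits against T0, which is a comparison of change scores. Using T0 as a covariate, or constraining the T0 means to be equal, gives a more precise estimate of the same treatment effect whenever the correlation between visits is below 1.

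The stake is power and clarity of the estimate on the primary outcomes, in a trial with about 38 to 42 patients per group. There is also a risk of misreading. The group main effect averages over a visit at which no effect can exist, and the text does not say that this term is not the treatment effect.

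**Working it through.** **Inputs from the document.** Difference 1.93, SD 6, power 80%, significance level 5%, 152 participants before dropout, four groups, 42 per group after dropout (5.1); two-sided test (5.2). 152 / 4 = 38 evaluable per arm.

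**Assumptions, not in the document.** Equal correlation rho between all visits, 0.5 with range 0.3 to 0.7; equal variance at each visit; SD 6 is the SD of a single-visit value (5.1 does not say whether it belongs to a value or to a change); two arms compared.

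**The plan's own figure.** n = 2 × [6 × (1.960 + 0.842) / 1.93]^2 = 151.7, so 152. The formula returns this as a number per arm, while 5.1 uses it as the trial total. That is a separate matter, but it is why power is low in every row below.

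**Variance factors, one post-treatment visit** (multiples of 6^2 = 36):
- change from T0: 2(1 - rho)
- T0-adjusted: 1 - rho^2 = (1 - rho)(1 + rho)
- ratio: 2 / (1 + rho), above 1 for every rho below 1

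The standard error of the group difference is 6 × sqrt(factor × 2/38). Power is from the noncentral t distribution, two-sided 5%.

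| rho | Factor, change | Factor, adjusted | Sample-size ratio | Power, change | Power, adjusted |
|---|---|---|---|---|---|
| 0.3 | 1.40 | 0.91 | 1.54 | 22% | 31% |
| 0.5 | 1.00 | 0.75 | 1.33 | 28% | 36% |
| 0.7 | 0.60 | 0.51 | 1.18 | 43% | 49% |

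The gain is 6 to 9 percentage points. Put in sample size, the change analysis needs 18% to 54% more patients for the same precision.

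**If SD 6 is the SD of a change.** The change analysis then has 28% power at any rho. The adjusted variance is 36 × (1 + rho)/2, which gives 40 / 36 / 32% at rho 0.3 / 0.5 / 0.7. The gain is 12, 8 and 4 points. The direction is the same.

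**If T1 and T2 are averaged** (the plan does not choose this). The factors are 1.5(1 - rho) for change and (1 + rho)/2 - rho^2 for adjusted. Power at 38 per arm is 27 / 36 / 54% against 46 / 50 / 64%.

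**The group main effect over T0, T1 and T2.** With no difference at T0 and a constant effect d at T1 and T2, its expectation is (0 + d + d)/3 = 2d/3, so 1.93 becomes 1.29. The variance factor is (1 + 2 rho)/3, and power at 38 per arm is 24 / 20 / 18%. This applies only if that term is read as the treatment effect.

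**The case against.** Four points can be made for the plan.

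First, a reader might infer that the model adjusts for DFU stage and nothing else. The document does not support that: the next sentence of 5.2 admits other clinical factors. What stands is narrower. Those factors are unspecified, and the baseline value of the outcome is not named among them.

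Second, a reader might infer that the plan's treatment estimate is biased downward by one third. That does not follow. Section 5.2 does not designate the group main effect as the treatment effect, and in a pre/post mixed ANOVA the natural treatment test is group-by-time. The planned effect sizes use T0 as a reference and do not average it in. The two-thirds figure also assumes the same effect at T1 and T2. It remains a conditional warning.

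Third, the group-by-time test is valid and uses the T0 data, only less efficiently. It would be wrong to say that the test discards the baseline or is biased. This is accepted, and the point concerns precision.

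Fourth, the size of the loss does not carry over uniformly to every outcome. Section 5.1 does not say which outcome the 1.93 and 6 describe. For DFU healing, baseline stage is always a covariate, and the PEDIS classification recorded at baseline overlaps with RESVECH in extent, depth and infection. Part of the adjustment may already be present there. DFU stage is much less likely to stand in for baseline quality of life or blood markers.

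It might also be said that the choice of term and covariates belongs in an analysis plan that is not shown. That covers the silence on the primary term. It does not cover the model and mandatory covariate that 5.2 itself fixes.

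**Conclusion.** The point holds as one of efficiency. As written, 5.2 compares groups over T0, T1 and T2 without adjusting for the T0 value of the outcome, although that value is scheduled in every arm. Under the stated assumptions this costs about 6 to 9 points of power at a single visit (8 points, 28% against 36%, at rho 0.5). The ordering holds for every rho below 1; the size depends on a correlation that the document does not give and on the reading of SD 6. The loss may be smaller for RESVECH. Baseline adjustment does not bring power near 80%, because the larger shortfall comes from the sample size. The shrinkage to two thirds is a consequence to rule out in the text and not a defect of the planned test. The change is worth making because it is nearly free.

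**What to change.** In 5.2, fit a longitudinal mixed model with T0, T1 and T2 as responses and the group means constrained to be equal at T0. This version should come first: it keeps the pre/post comparison of aim (ii) and retains patients who have only a T0 value, in line with the intention-to-treat approach. The alternative is to model T1 and T2 as responses with group, visit and group-by-visit, and with the same outcome's T0 value and its interaction with visit as covariates. In either case keep DFU stage, and state that the treatment effect is the adjusted between-group difference at T1 and at T2, not the main effect over T0 to T2.

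The cost is a few degrees of freedom and slightly more analysis work in software already named (R, SPSS). No added patients, visits or measurements are needed. With the covariate version, patients without any post-baseline value drop out of the model, and aim (ii) needs its own analysis.

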### 2.3. Participant Recruitment and Selection Criteria

Patients with chronic DFU attending the first consultation of the multidisciplinary outpatient clinical of diabetic foot ulcer from three major hospitals in Northern Portugal will be recruited. In the first consultation, researchers (Researchers 1, 2, and 3) will collect the clinical information of each patient to signalize those that meet eligibility criteria. Patients will be consecutively enrolled in the study.

The inclusion criteria are: (i) being 18 years old or more, (ii) having one or two diabetic chronic ulcers (a non-healing ulcer for six or more weeks and less than 12 weeks; in case of patients with two active chronic DFUs, the ulcer with the largest area will be selected as the index ulcer) at the time of baseline assessment, (iii) reporting clinical levels of psychological distress, and iv) providing written informed consent. Clinical distress is assessed according to the Hospital Anxiety and Depression Scale (HADS) [33] and the Perceived Stress Scale (PSS) [34], with patients scoring ≥11 on the HADS subscales or ≥13 (male patients) and ≥17 (female patients) on the PSS evaluated as being clinically distressed.

Exclusion criteria include: (i) the DFU, at the time of baseline assessment, being a relapse; (ii) having three or more DFUs at the time of baseline assessment; (iii) having undergone a transplant; (iv) being on hemodialysis treatment; (v) having a cancer disease; (vi) having degenerative dementia or severe psychiatric illness (e.g., schizophrenia), (vii) receiving psychological counseling, or (viii) taking psychiatric medication during the study period.

For the qualitative study, participants that completed at least 75% of the intervention sessions or placebo sessions (active control group) will be invited to participate, together with their family caregiver. Participants will be purposively selected according to the type of diabetic foot (neuropathic versus neuroischemic) and DFU progression (positive versus negative). The sample will also be selected according to participants’ capacity to provide in-depth and rich-textures information regarding the intervention’s effectiveness since qualitative purposive sampling is considered to be more efficient than random sampling [35]. Thus, the quantitative study sample will include four single-per-participant interviews per group (4 conditions × 3 groups), in a total of 12 patients’ interviews and 12 caregivers’ interviews.

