### 2.4. Randomization

All eligible patients will be randomly assigned to one of the four groups—TG1, TG2, ACG, or PCG—in varying size blocks so that, over time, all groups can have a similar number of participants [36,37]. An independent researcher (Researcher 4), unaware of the numeric coding for each group, will create the randomization sequence using an online random number generator (https://www.graphpad.com/quickcalcs/randomize1/, accessed on 15 December 2021) with a 1:1 allocation, using random block sizes of 12. Researchers 2, 3, and 4 are blind to the block size used in the randomization procedure.

A priori stratification was defined considering the three hospitals where data collection will take place, as well as two common comorbid conditions deemed as factors of poor prognostic outcomes in patients with DFUs, specifically chronic kidney disease (CKD) and peripheral arterial disease (PAD) [38,39], to ensure that distribution of patients between groups is balanced in terms of confounders. Thus, randomization is stratified according to (i) hospitals; (ii) CKD and its disease stages (without CKD/CKD stage 1 and 2/CKD stage 3 and 4); and (iii) PAD (without PAD/with PAD), in a total of 12 possible strata.

Participants’ blinding will be maintained throughout the conduct of the trial, whereas Researchers 1, 2, and 3 will be aware of the allocation since they are responsible and will conduct the TG1 and ACG sessions. Quantitative data analysts will be blinded to participant allocation. The randomization process will be conducted at the end of each week to reduce the time interval between the randomization and the beginning of interventions.

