### 4.2. Adherence to the Treatment Plan

Patients will be fully informed about the study goals, procedures, and potential benefits that may arise from the results of the DFU treatment. Assessment moments, intervention, and placebo sessions will be scheduled for diabetic foot appointment days so that patients will not have to go to the hospital on purpose to participate in the study. Before the appointment day, Researchers 1, 2, and 3 will call patients to remind them of their appointment with the research team for the purpose of the study. Participants will be asked to complete the last assessment (T2) even if they miss the mid-term assessment (T1).

To engage the health professional staff (e.g., physicians, nurses, podologists), meetings will be held with the physicians responsible for the multidisciplinary consultation of diabetic foot and head nurses (in the three hospitals involved in the study), in order to introduce the study and clarify any questions that may arise.

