## Figures and Tables

**Figure 1 ijerph-19-08556-f001:**
[figure not shown]
Study design and CONSORT flow chart.

**Table 1 ijerph-19-08556-t001:** Schedule of enrollment, interventions, and assessments of the PSY-DFU study, following the Standard Protocol Items Recommendations for Interventional Trials (SPIRIT) guidelines.

TIMEPOINTS	Enrollment	Allocation	Pos-Allocation			Follow-Up
		T0	T0	T1	2 Weeks after T1	T2
Eligibility	X					
Informed consent	X					
Allocation		X				
INTERVENTIONS			[figure not shown]			
PMR + GI (TG1)						
H + GI (TG2)						
Control groups			[figure not shown]			
Active (ACG)						
Passive (PCG)						
ASSESSMENTS						
Sociodemographic data			X			
Health literacy			X			
Clinical data (PEDIS)			X	X		X
DFU evolution/healing ^a^			X	X		X
Impact of DFU on QoL			X	X		X
Mental and physical QoL			X	X		X
Perceived stress			X	X		X
Psychological morbidity			X	X		X
DFU representations ^a^			X	X		X
Blood pressure ^b^			X	X		X
Heart rate ^b^			X	X		X
Biochemical parameter			X	X		X
Inflammatory markers			X	X		X
Angiogenic markers			X	X		X
miRNAs			X	X		X
Immune cells			X	X		X
Semi-structured interviews					X	

QoL—quality of life; PMR + GI—progressive muscular relaxation with guided imagery; H + GI—hypnosis with guided imagery; ACG—active control group; PCG—passive control group; PEDIS—Perfusion, Extent, Depth, Infection, and Sensation; DFU—diabetic foot ulcer. ^a^ In T1 and T2, when the DFU is healed, the DFU progression and DFU representations are not assessed. ^b^ Blood pressure and heart rate are assessed before and after each intervention (PMR + GI and H + GI) and placebo (ACG) session.

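### Section 5.2 names a repeated-measures ANOVA that, in its usual form, loses patients with a missed visit or an unscored healed ulcer, and it does not commit to the stratification factors

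*Protocol article*

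**What the plan says.** On population, Section 5.2 states that "an intention-to-treat approach will be assumed to evaluate the impact on the primary and secondary outcomes". On the model, the comparison of treatment and control groups over time "will be performed through mixed general linear models of analysis of variance for repeated measures". R and SPSS are the named software.

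On covariates, Section 5.2 says "All previous analyses will include the DFU stage at the baseline as a control variable", and then "Other confounding clinical factors associated with the outcome variables will also be considered in the statistical analysis". Section 2.4 says "randomization is stratified according to (i) hospitals; (ii) CKD and its disease stages", with PAD as the third factor, and describes CKD and PAD as markers of poor prognosis.

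On incomplete data, Section 4.2 says "Participants will be asked to complete the last assessment (T2) even if they miss the mid-term assessment (T1". Footnote a of Table 1 says "In T1 and T2, when the DFU is healed, the DFU progression and DFU representations are not assessed". Section 3.3.1 defines a RESVECH score of 0 as complete healing, and healing is a primary outcome.

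**The concern.** Three statements do not fit together comfortably. The plan analyses patients as randomised, it asks for a T2 visit even when T1 was missed, and it names a model whose classical form uses only patients with T0, T1 and T2. Run that way, the T2 data are collected and then discarded, and membership of the analysis depends on behaviour after randomisation. Section 7 reports low compliance in the treatment groups as a difficulty already met, so loss that differs by arm is plausible.

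The healed-ulcer footnote matters more for bias. If no 0 is entered, the patients who go missing on a primary outcome are the successes, and an arm that heals more patients loses more of its best results.

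The covariate issue is separate. Stratified randomisation balances the arms on hospital, CKD and PAD, but an analysis that leaves these out does not take credit for that balance, so its standard errors are too large. Choosing further covariates by their association with the outcome also leaves the adjusted model open until the data are seen.

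**Working it through.** **Inputs from the protocol article.** Planned total 169, 42 per group, dropout 11%, difference 1.93, SD 6 (Section 5.1); strata of three hospitals, three CKD levels and PAD yes/no (Section 2.4). The 11% is a dropout rate for intervention sessions; no rate for missed assessments is given, so its use below is an assumption.

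**The plan's own figure.** 2 × 6² × (1.96 + 0.84)² / 1.93² = 151.5, rounded up to 152, and 152 × 1.11 = 168.7, i.e. 169. The figures reproduce. The formula gives 152 per arm, not in total; that is a separate point, and it costs more power than anything here.

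**Step 1: loss under complete-case analysis.** Let m be the proportion missing each of T1 and T2. The complete fraction is 1 − m if the same patients miss both visits, and (1 − m)² if misses are independent. Power is for one pair of arms, difference 1.93, SD 6; with no loss (42 per arm) it is 31.4%.

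| m (assumed) | Same patients: complete of 169 | Power | Independent: complete of 169 | Power |
|---|---|---|---|---|
| 11% | 0.89 × 169 = 150 | 28.5% | 0.792 × 169 = 134 | 25.8% |
| 20% | 0.80 × 169 = 135 | 26.1% | 0.64 × 169 = 108 | 21.7% |
| 30% | 0.70 × 169 = 118 | 23.4% | 0.49 × 169 = 83 | 17.7% |

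At 11% the loss is therefore 11% to 21%.

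**Step 2: what a likelihood model recovers.** It keeps patients with one of the two post-baseline visits. Under independence at 11%, only 0.11² = 1.2% have neither, so about 167 of 169 contribute rather than 134. If the same patients miss both visits, it recovers nothing on the post-baseline comparison.

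**Step 3: healed ulcers.** In an illustrative simulation (assumed baseline mean 15, SD 6, correlation 0.5, scores floored at 0, 42 per arm), patients healed at T1 or T2 were either scored 0 or dropped.

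| Healed, control / treatment | T2 difference, healed scored 0 | T2 difference, healed dropped |
|---|---|---|
| 6% / 11% | 1.82 | 1.48 |
| 13% / 22% | 1.67 | 1.23 |
| 27% / 39% | 1.40 | 0.94 |

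The difference shrinks by about 19%, 27% and 33%. A likelihood model alone does not cure this, because it would predict the healed patients from the unhealed ones.

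**Step 4: stratification factors.** If the strata explain a share R² of outcome variance beyond ulcer stage, leaving them out inflates the standard error by 1/√(1 − R²).

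| R² (assumed) | Standard error ratio | Power at 38 per arm (28.8% unadjusted) |
|---|---|---|
| 0.02 | 1.010 | 29.3% |
| 0.05 | 1.026 | 30.1% |
| 0.10 | 1.054 | 31.5% |
| 0.20 | 1.118 | 34.7% |

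**Step 5: baseline score as covariate.** A change from T0 has variance 2σ²(1 − ρ); adjustment for the T0 score gives σ²(1 − ρ²). At an assumed ρ = 0.5 these are σ² and 0.75σ², so the standard error falls by 1 − √0.75 = 13%, less where ulcer stage already carries the same information.

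**The case against.** A reader might infer that the plan drops every patient with a missed visit. The article does not say so. It states no deletion rule, the word mixed also fits a likelihood model, both named packages can fit one, and handling of incomplete cases is commonly left to an analysis plan, which is not shown here. Asking for T2 after a missed T1 supports intention-to-treat. This stands as far as it goes: loss of patients follows from the usual form of the named model, not from a stated rule. What remains is that the article names a model whose ordinary meaning conflicts with its own population.

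A reader might also infer that omitting the strata undoes intention-to-treat. It does not, because covariates do not change who is analysed, and the resulting standard errors err on the cautious side. Nor are CKD and PAD ruled out. They can enter as other clinical factors, and if ulcer stage means the PEDIS system of Section 3.2.2, its perfusion component covers PAD in part. Hospital is not a clinical factor and has no such route.

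Finally, exclusion (viii), "taking psychiatric medication during the study period", might be read as removing randomised patients who start such medication later. It stands in a list of eligibility criteria, nothing says that patients are removed after randomisation, and the intention-to-treat sentence points the other way. The wording is loose, but the documents do not support calling it an error.

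On size, 11% is a session-dropout rate, and if the same patients miss both visits the loss is only the 11% the sample size already allows for.

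**Conclusion.** The point holds as a call to fix the model, not as proof that patients will be dropped. As named, the analysis would in its standard form omit patients without all three scores, against the stated intention-to-treat approach and the T2 collection in Section 4.2. At an assumed 11% missing per visit that is 11% to 21% of patients, and pairwise power falls from 31% to between 26% and 29%. Leaving healed ulcers unscored is the part most likely to bias a primary outcome, but its size rests wholly on assumed inputs, and it disappears if 0 is entered. Not committing to hospital, CKD and PAD is a matter of precision: standard errors about 5% to 12% too large if the strata explain 10% to 20% of variance, and less at lower R² or with overlap with ulcer stage. None of the missingness or R² values comes from the document.

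**What to change.** Change Section 5.2 as follows.

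- Name a likelihood-based linear mixed model for T1 and T2 with arm, visit, arm × visit and unstructured covariance, keeping all randomised patients with available data. Report by arm how many have neither visit, since they add nothing to the comparison.
- Adjust for the baseline value of the outcome, hospital, CKD level, PAD and baseline ulcer stage. Use the CKD levels actually used in randomisation: 3 × 3 × 2 gives 18 strata, while Section 2.4 states 12.
- Include the stratification factors in the Cox models, collapsing sparse levels.
- Enter RESVECH 0 at any visit where the ulcer is recorded as healed.
- In the between-arm comparison, confine covariates chosen for their association with the outcome to a labelled sensitivity analysis. The covariates that aim (ii) in Section 2.1 names for the pre-post comparison stay.

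The cost is wording and a few degrees of freedom: 2 for hospital, 2 for CKD, 1 for PAD and 1 for the baseline score, 6 in all as main effects. The data and software are already in the plan. Entering zeros puts a cluster of scores at the floor, so the residuals should be checked; the planned time-to-healing analysis complements the score.

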#### 3.4.1. Perceived Stress

The overall stress perceived by patients will be assessed through the Perceived Stress Scale (PSS) [34], a self-reported measure to be answered by participants.

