## 4. Interventions

### 4.1. Trial Arms

All participants will receive standard of care medical/nursing treatment for DFU, according to the guidelines of the Portuguese General Health Direction [46] and the International Working Group on the Diabetic Foot [47].

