## 5. Statistical Analysis

### 5.1. Sample Size

Using Sakpal’s formula [49] and according to the descriptive results of the pilot study [50], considering the difference in the mean (1.93) and standard deviation (6) of the treatment versus passive control groups, with a statistical power of 80% and a statistical significance level of 5%, a definitive RCT will require 152 participants. Considering a dropout rate for intervention sessions of 11%, a definitive RCT with four groups will require a sample size of 169 participants, with 42 patients per group [49].

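### Visit-to-visit effect sizes and an uncontrolled pre-post primary aim are given the job of showing a treatment effect, beside a valid between-arm model

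*Protocol article*

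**What the plan says.** Section 5.2 (Data Analysis) assigns the main comparison to a model: "The comparison between the treatment groups versus control groups over time (differences between and within) will be performed through mixed general linear models". It then says that Cohen's d will also be provided "between T0 and T1, T1 and T2, and T0 and T2 to determine if the intervention shows any treatment effect". That sentence names pairs of visits and no control group.

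The Primary Specific Aims contain both kinds of comparison. Aim (i) compares the two treatment groups with the control groups. Aim (ii) is "to compare patients pre and post-intervention in the TG1 and TG2", adjusted for health literacy, clinical characteristics and sociodemographic variables, with no control group.

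Three other parts of the article bear on what a before-after contrast would contain:

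- Section 4.1: "All participants will receive standard of care medical/nursing treatment for DFU".
- Section 4.1.2: the active control group (ACG) is there to account for attention, because contact with the therapists may itself help healing.
- Section 2.3: patients qualify as distressed "with patients scoring ≥11 on the HADS subscales or ≥13 (male patients) and ≥17 (female patients) on the PSS". Sections 3.4.1 and 3.4.2 use the same two scales as secondary outcomes.

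**The concern.** A standardised change from one visit to the next within an arm is the sum of the treatment effect and everything else that happens over that interval. Only a contrast with a concurrent randomised arm separates the two. The covariates in aim (ii), and the baseline ulcer stage for which Section 5.2 adjusts, describe who the patients are. They do not separate treatment from time, so adjusting for them does not cure the problem.

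What is at stake is the conclusion. A report that follows the text could show a moderate T0-T1 effect size in TG1 or TG2, cite the protocol's own statement of purpose, and call it a treatment effect while the between-arm contrast shows nothing.

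**Working it through.** **1. The plan's own benchmark.** Section 5.1 plans on "considering the difference in the mean (1.93) and standard deviation (6) of the treatment versus passive control groups", so the standardised between-group difference is 1.93 / 6 = 0.32. With 80% power and two-sided 5%, these inputs give n = 2 × (1.960 + 0.842)² × 6² / 1.93² ≈ 152. The plan's figure reproduces, as a number per arm of a two-arm comparison. Nothing below depends on it, except that 42 per arm then gives about 31% power for a pairwise difference of that size.

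**2. What each stated contrast contains if the intervention has no effect.**

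| Source of change | Where documented | Within-arm d | Between-arm d |
|---|---|---|---|
| Healing under standard care | Section 4.1 | included | cancels in expectation |
| Attention from therapists | Section 4.1.2 | included | cancels against ACG, not against the passive control group (PCG) |
| Regression to the mean (PSS, HADS) | Sections 2.3, 3.4.1, 3.4.2 | included | cancels in expectation |

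**3. Regression to the mean, PSS, selection on PSS alone.** Assumed, not in the documents: population mean 16, SD 7, retest correlation 0.7. The cut-off of 17 (women) is from Section 2.3.

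- z = (17 − 16) / 7 = 0.143; φ(z) / (1 − Φ(z)) = 0.891.
- Mean of those selected: 16 + 7 × 0.891 = 22.24.
- Expected fall with no treatment: (1 − 0.7) × 6.24 = 1.87 points.
- d on the population SD: 1.87 / 7 = 0.27.
- SD of those selected: 7 × √(1 + 0.143 × 0.891 − 0.891²) = 4.04; d = 1.87 / 4.04 = 0.46.

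With retest correlation 0.6 to 0.8 and cut-offs 13 and 17, the spurious d runs from 0.11 to 0.62.

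**4. The same under a HADS-or-PSS rule.** A patient admitted on HADS may have a low PSS, which dilutes the effect. Further assumptions: PSS-HADS correlation 0.5 to 0.7, 30% to 50% HADS-positive, and follow-up PSS depending on baseline PSS only. Retest correlation stays at 0.7.

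| Cut-off | d, population SD | d, SD of those selected |
|---|---|---|
| 17 | 0.14 to 0.22 (from 0.27) | 0.16 to 0.33 (from 0.46) |
| 13 | 0.11 to 0.15 (from 0.16) | 0.14 to 0.22 (from 0.24) |

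**5. A common improvement in a healing score.** The documents give no control-arm healing rate, so this is purely illustrative. Suppose the score falls by 1.93 points in every arm, with SD 6 and within-patient correlation 0.3 to 0.7. The before-after d is 1.93 / 6 = 0.32, the same as the planned between-group effect. The paired standardised change is 1.93 / (6 × √(2(1 − ρ))), that is 0.27 to 0.42. With 42 patients a paired test is then significant in about 41% to 75% of trials, with no treatment effect at all. The between-arm test is significant in 5%.

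**The case against.** The strongest reply is that the article already plans the right analysis. The mixed model compares treatment with control over time, aim (i) is stated against controls, the analysis is by intention to treat, and the effect sizes are only an addition. That stands. A reader might infer that the plan discards the four-arm randomisation, or that before-after effect sizes alone will decide efficacy. The text supports neither.

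A second reply is that the effect-size sentence follows a treatment-versus-control sentence and could mean d for the between-group difference in change over each interval. That reading is possible but is not stated, and aim (ii), a separate pre-post aim within TG1 and TG2, favours the before-after reading. It is also fair to say that an article may leave the formula for d to a fuller document. The problem here is what the sentence does state: contrasts between visits, with the purpose of determining a treatment effect.

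Third, the numbers are soft, and this stands too. PSS and HADS are secondary outcomes, so regression to the mean from the distress cut-off reaches the primary outcomes only indirectly. Selection on PSS alone overstates it for this trial's entry rule. Entry requires an ulcer that has not healed for at least six weeks, so improvement in every arm is plausible but not documented. The closest support is Section 7, which says treatment-group sessions end when the ulcer heals completely; that says nothing about the control arms. Finally, Section 5.1 does not name the outcome behind 1.93 and 6, so 0.32 is a yardstick of scale and not a like-for-like comparison with a PSS change.

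**Conclusion.** The point holds as a defect in a stated rule, limited in reach. Alongside a valid between-arm model, Section 5.2 and aim (ii) give uncontrolled change over time the standing of evidence for efficacy. Under no treatment effect that change need not be zero, whereas the between-arm contrast has expectation zero.

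Its size cannot be read from the documents. For PSS, under the assumptions shown with retest correlation 0.7 and cut-off 17, the spurious d is 0.27 to 0.46 if selection is on PSS alone, and about 0.14 to 0.33 under a HADS-or-PSS rule. For healing and ulcer-related quality of life, the direction depends on how patients do under standard care and attention, which the article does not quantify. The correction should be made, but it does not call the planned randomised comparison into question.

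**What to change.** - **Section 5.2, effect sizes.** Define d as the between-arm difference (each treatment group against ACG, each against PCG, and TG1 against TG2) in baseline-adjusted means at T1 and T2, divided by the pooled baseline SD, with a 95% CI.
- **Section 5.2, conclusions.** State that conclusions about a treatment effect rest on the between-arm (group-by-time) contrasts. Label within-arm change between visits as descriptive.
- **Aim (ii).** Reword it as a baseline-adjusted between-arm comparison, or keep the pre-post description without presenting it as a test of efficacy.
- **If a between-group d was already intended,** the sentence should say so; the same edit covers it.

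The cost is wording in two places. The estimates come from the planned mixed model and the scheduled visits, with no new data, visits or patients.
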